## Abstract

Introduction: Responsive caregiving is one of the most fundamental pillars of early childhood development. In the newborn stage, the parents are undergoing transitions and require support to understand the nuances of interacting with the young baby. The role of healthcare facilities in this becomes vital as a hub for conducting parenting education sessions that may yield thriving outcomes for young children and their future development. This study aims to explore the impact of the early childhood newborn parenting program on parental confidence and newborn responsive interaction and to explore the perceptions of healthcare providers regarding the intervention implemented in healthcare settings.

Methods: An implementation research design will be used in this study. A total of 500 participants will be included in the study, 400 from Pakistan and 100 from Afghanistan. There are two sites: each site will be randomly assigned as a control or an intervention. The rationale was to ensure that both sites are in different geographical locations. Participants from each side will be chosen using a convenience sampling technique. Cohort 1 (control group) will only be provided with a self-study, one consolidated handout on responsive caregiving, and one-time bed teaching, and will be requested to visit the center after six months (child age) for an endline. While cohort 2 (intervention group) will be provided a six-module intervention consisting of one session at birth with a self-study handout on responsive caregiving, and five monthly sessions (once a month till the infant turns six months) will be conducted. Outcomes measured at the baseline and endline (at six months) include differences in responsive interactions and parenting confidence scores between the control and intervention groups using tools such as Karitine parenting confidence, responsive interaction scale, Caregiver Reported Early Development Instruments (CREDI), WHO QoL, and Patient Health Questionnaire (PHQ).

Results: This is an ongoing study protocol, and the analysis of the results is expected in December 2025.

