## Materials and methods

Study design

This before-and-after implementation feasibility study will examine the feasibility, fidelity, and adaptation of this intervention in the primary healthcare settings of remote Pakistan and Afghanistan. Implementation research is a relatively new approach in the medical sciences, but it has been widely used in various global, public health, and social sciences research. It also has great potential to allow flexibility for the researchers to be engaged and involved in the process of research. The field sites will be conveniently divided into two groups. The intervention and the control. The intervention group will undergo a structured responsive parenting education program, i.e., six sessions in the first five months of life on a structured curriculum under the supervision of trained lady healthcare workers, while the control group will undergo limited intervention, i.e., a compiled handout at birth for self-study (outlined in Figure 1). 

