**Figure 1 FIG1:**
[figure not shown]
Flow chart of the study procedure

Study setting

Participants will be recruited from the six basic health centers (BHCs) of not-for-profit private healthcare systems in Pakistan and Afghanistan. These BHCs will be chosen as primary healthcare facilities to pilot the intervention, as shown in Tables 1-2. The BHCs provide maternal, newborn, and child health services (MNCHS), including antenatal care, delivery, and postnatal care (ANC-PNC), family planning, immunization, adult health screening, and regular growth monitoring of <3 years old. Through lady health visitors (LHVs), responsive parenting education will be integrated into their maternal and newborn care model.

**Table 1 TAB1:** Field sites (Pakistan) F4HE: Foundations for Health and Empowerment

S/n	Site Selection	Location of Health Facility	Type of Health Facility	Level of Services	Average Deliveries Per Month	Covering Under F4HE Geographical Areas
1	Pakistan Intervention Group Site 1 (PIGS 1)	District Upper Chitral	Basic Health Center	Primary	10	Yes
							Pakistan Intervention Group Site 2 (PIGS 2)	District Lower Chitral	Basic Health Center	Primary	4	Yes
	2	Pakistan Control Group Site 1 (PCGS 1)	District Upper Chitral	Basic Health Center	Primary	10							Yes
							Pakistan Control Group Site 2 (PCGS 2)	District Lower Chitral	Basic Health Center	Primary	4	Yes	

**Table 2 TAB2:** Field sites (Afghanistan) F4HE: Foundations for Health and Empowerment

S/n	Site Selection	Location of Health Facility	Type of Health Facility	Level of Services	Average Deliveries per Month	Covering Under F4HE Geographical Areas
							1	Afghanistan Intervention Group Site 1 (AIGS 1)	Baharak District	District Hospital (DH)	Primary and Secondary	265	Yes
							2	Afghanistan Control Group Site 1 (ACGS 1)	Jurm District	Comprehensive Health Center (CHC)	Primary	77	No

Eligibility criteria

Inclusion criteria for the study enrolment are (i) the newborn’s mother following a normal delivery; (ii) the newborn does not exhibit any underlying morbidities; (iii) the family is not living in ultra-poverty with less than 15,000/- total household income; and (iv) the family can understand Urdu. The exclusion criteria for the study include (i) newborns with underlying conditions or morbidities, (ii) the family living on a 15,000 household income per month, and (iii) mothers with postpartum depression.

Study intervention

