A total of 500 participants will be chosen, 100 from four primary healthcare facilities in the regions of Chitral, Pakistan, and 100 from two primary healthcare facilities in Afghanistan. A total of 200 before-intervention participants as a control group and 200 intervention participants in Pakistan will be recruited. Similarly, for Afghanistan, 50 pre-intervention (control) participants and 50 intervention participants will be recruited as a control group. The sample size is chosen based on convenience sampling, and the facilities are selected considering the number of deliveries and outreach feasibility. It is anticipated that 40% of the total annual deliveries may consent to participate, and based on calculations, this will help us achieve our N for each of the cohorts. Additionally, there might be variations in the actual data collection.

Data collection plan

We will have two cohorts: a cohort before the intervention and an after-cohort with the intervention. Each cohort will last for six months.

Cohort 1 (control group): Baseline data will be collected, and they will be provided with a self-study pictorial module. They will be tracked and requested to visit the center at six months (child age) post-delivery. At six months, their endline data on responsive interactions, parenting confidence, and patient experience will be collected.

Cohort 2 (intervention group): Baseline data will be collected, and they will be provided a six-month intervention consisting of one session at birth with a self-study manual, and five monthly sessions (once a month till the infant turns six months). At six months, they will also be assessed on the measures mentioned above, and endline will be collected.

Data analysis

Both qualitative and quantitative data analysis strategies will be used to conduct data analysis.

Quantitative analysis will be performed using the statistical package for the social sciences (SPSS Inc., Chicago, IL). Descriptive statistics, such as frequencies, percentages, means, and SD, will be computed for demographic characteristics, QoL, and parental outcomes (confidence, feeding, and teaching assessment using KPSC, NBRI score). Independent sample t-test, paired test, and repeated measure ANOVA will be used to compare within and between-subject effects. Multilevel logistic regression will also be performed for categorical outcomes to observe the effectiveness after controlling for the confounding factors. P≤0.05 will be considered significant.

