There will be a structured training whereby internationally trained master trainers in ECD and Keys to Infant Caregiving from Parent-Child Relationship Programs, at Barnard Center, University of Washington and internally certified on ECD PREP ObGyn Aga Khan University curriculum, will provide training to the field site investigators and coordinators, who will then cascade the training to the lady healthcare workers at each study setting. After receiving training, the trained healthcare providers will deliver the content in group-based teaching sessions. Each lady healthcare worker will be selected based on their prior experience in patient and family education by the healthcare facility lead and will undergo a four-day structured training program. Additionally, they will have monthly mentoring check-ins throughout the intervention and will be provided with constant support and random first-hand check-ins by the field coordinators, who will go and co-conduct and observe the session with them. The whole intervention will be closely supervised by the field co-investigators and the lead investigator. An assigned research specialist will conduct monthly meetings to provide the support needed at the field sites.

Ethical considerations

This proposal has received approval from the National Bioethics Commission (No.4-87/NBCR-986/23/323), Pakistan, the Aga Khan University ethical review committee (ERC # 2023-8343-24153), and the Institutional Review Board of Afghanistan (IRB Code No: A-8-24-445). Informed written consent will be sought from all the participants. They will be informed about all the modalities involved in the research project, their rights, and, in no form, will there be names or any identifiable information that will be sought or recorded. All forms will have a unique participant code. All the data will be kept confidential. The data collectors will collect the forms, seal the forms, and send them to the main institution. Additionally, the data will be kept in lock and key. Until the forms are sent here, all the data on the field sites will also remain in a locked drawer.

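### Whole facilities are assigned to the arms, but the scale scores are compared between arms with individual-level tests at P≤0.05, so any between-facility variation makes those tests anti-conservative

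*Protocol article*

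**What the plan says.** **Assignment.** The Abstract says "each site will be randomly assigned as a control or an intervention", while Study design says "The field sites will be conveniently divided into two groups". The two accounts disagree on random against convenience allocation, but in both the unit is the site. Tables 1 and 2 list six facilities: two intervention and two control in Pakistan, one of each in Afghanistan. Sample size, recruitment, and enrolment plans 200 mothers per arm in Pakistan and 50 per arm in Afghanistan.

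**Delivery.** Trained facility workers "deliver the content in group-based teaching sessions" (Delivery of the intervention).

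**Analysis.** For the scale scores, "Independent sample t-test, paired test, and repeated measure ANOVA will be used to compare within and between-subject effects". The only model that could carry a facility term is for another type of outcome: "Multilevel logistic regression will also be performed for categorical outcomes". The significance threshold is P≤0.05. No ICC, design effect or facility term appears for the continuous scores.

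**The concern.** Parenting confidence and responsive interaction, the lead outcomes, are scale scores. An independent t-test treats each mother as a separate unit. Mothers at one facility share staff and catchment and, in the intervention arm, teaching groups, so their scores are likely to be correlated. A between-arm standard error that ignores this is too small, and an ordinary difference between facilities may be read as an effect of the programme.

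The article's own tables show that facilities differ. In Afghanistan the intervention site is a district hospital giving primary and secondary care, with 265 deliveries a month, inside the project's area. The control site is a primary-level health center with 77 deliveries a month, outside that area. At stake is the validity of the between-arm P values, on which the first research objective depends.

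**Working it through.** **Inputs from the article**
- Facilities per arm: 2 in Pakistan, 1 in Afghanistan (Tables 1 and 2).
- Planned mothers per arm: 200 and 50. An equal split gives 200/2 = 100 per Pakistan facility.
- Monthly deliveries at the two Pakistan facilities of each arm: 10 and 4 (Table 1). Expected consent: 40% of annual deliveries.
- Threshold 0.05, taken as two-sided because the article does not say.

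**Assumed:** the ICC, shown from 0.001 to 0.05, equal in both arms.

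**Implied cluster sizes.** 10 × 12 × 0.40 = 48 and 4 × 12 × 0.40 = 19.2, so about 48 and 19 mothers per facility in a year. That is about 67 per arm against the planned 200.

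**Formulas**
- Design effect within an arm: DEFF = 1 + ICC × (Σm²/Σm − 1), with m the mothers per facility.
- True two-sided error of the nominal 5% test: 2 × [1 − Φ(1.96/√DEFF)].

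**Reproducing the nominal level.** At ICC = 0, DEFF = 1 and the error is 5.0% (simulated 5.1% to 5.2%). The stated threshold holds only if there is no facility effect.

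**Multipliers of the ICC**
- Pakistan, 100/100: 20,000/200 − 1 = 99.
- Pakistan, 48/19: (2,304 + 361)/67 − 1 = 38.8.
- Pooled, 100/100/50: 22,500/250 − 1 = 89.

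**Results for an endline t-test (DEFF, then true error)**

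| Assumed ICC | Pakistan 100/100 | Pakistan 48/19 | Pooled 100/100/50 |
|---|---|---|---|
| 0.001 | 1.10, 6.2% | 1.04, 5.4% | 1.09, 6.0% |
| 0.005 | 1.50, 10.9% | 1.19, 7.3% | 1.45, 10.3% |
| 0.01 | 1.99, 16.5% | 1.39, 9.6% | 1.89, 15.4% |
| 0.02 | 2.98, 25.6% | 1.78, 14.1% | 2.78, 24.0% |
| 0.05 | 5.95, 42.2% | 2.94, 25.3% | 5.45, 40.1% |

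Simulating the t-test with random facility effects (8,000 runs per setting) gave 17.1% and 42.6% for Pakistan 100/100 at ICC 0.01 and 0.05, and 15.8% and 40.6% pooled. At planned sizes the Pakistan error doubles at an ICC of about 0.004 and triples at about 0.009.

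**Other splits.** Dividing the planned 200 in the 10:4 delivery ratio (143/57) gives 18.4% at ICC 0.01 and 45.5% at 0.05.

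**Check of the remedy.** A t-test on facility means brings the simulated error back to 5.0% to 5.1% for Pakistan (2 v 2) and 4.7% to 5.0% pooled (3 v 3), at ICC 0, 0.01 and 0.05.

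**Which tests are affected.** The figures apply to the endline comparison. For group-by-time effects the relevant ICC is that of the change from baseline, which may be smaller. The paired test compares each mother with herself within an arm. It is not a between-arm comparison and is not affected in this way.

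**The case against.** **The size is assumed.** This stands. A reader might infer that false positives are several times 5% as a matter of fact. The article gives no ICC, and at 0.001 the inflation is trivial. The cluster size matters too: at 48 and 19 mothers the error is just under twice nominal at ICC 0.01. If the six-month cohort length describes recruitment, clusters are about 24 and 10 and the error is about 7%, 9.5% and 16% at ICC 0.01, 0.02 and 0.05.

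**It is a feasibility study.** The article describes itself so, calls the design quasi-experimental and recommends a later randomised trial. That lowers the confirmatory weight. But it also aims to show impact, compares cohorts, speaks of effectiveness and sets a significance rule.

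**The controls may be an earlier cohort.** The sample size and data collection sections describe before and after cohorts. Tables 1 and 2 still name separate control facilities, so clustering by facility remains.

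**The analysis plan may settle it.** The article does not leave the matter open. It names the tests, sets the threshold and confines multilevel modelling to categorical outcomes. A plan that follows this text inherits the problem.

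Two stronger readings are not supported. A reader might argue that so few facilities rule out a significant randomisation test. That needs random allocation, and for a paired test a matching scheme; the article contradicts itself on the first and describes none of the second. A reader might also call the planned confidence intervals invalid, but the article plans none.

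**Conclusion.** The point holds in conditional form. Assignment is by facility, the stated between-arm tests of the scale scores ignore facility, and nothing else in the article cures this. The direction is certain if facilities vary at all; the size is not. For an endline t-test in Pakistan, ICCs of 0.01 to 0.05 give a true error of about 17% to 42% at planned sizes and about 10% to 25% at the sizes implied by the delivery and consent figures. Pooled at planned sizes the range is about 15% to 40%. Group-by-time tests may be inflated less.

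Afghanistan is a separate limit. With one facility per arm, arm and facility are fully confounded, and no reanalysis of that country alone can separate them.

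**What to change.** 1. For between-arm comparisons of the scale scores, replace the individual-level tests with a baseline-adjusted analysis that respects facility. This can be facility-level summaries, or a linear mixed model with country fixed, facility random and small-sample degrees of freedom.
2. Add a table of standard errors inflated for a range of ICCs, including low values.
3. Report estimates with intervals and drop P≤0.05 as the criterion of effectiveness.
4. Report Afghanistan alone descriptively and state the confounding.
5. Reconcile the Abstract and Study design on random against convenience allocation.

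**Cost.** Only the wording changes, but the intervals will be wide. Pakistan (2 v 2) leaves 4 − 2 = 2 degrees of freedom, critical t 4.30. An unstratified pooled comparison (3 v 3) leaves at most 6 − 2 = 4, critical t 2.78, and country or pair terms reduce that further. On unadjusted facility means at planned sizes, the difference detectable with 80% power in Pakistan rises from 0.28 SD, when clustering is ignored, to about 0.80, 0.97 and 1.38 SD at ICC 0.01, 0.02 and 0.05. Pooled, it rises from 0.25 SD to about 0.47, 0.56 and 0.77 SD. A significance claim becomes unlikely, which reflects what six facilities can show.

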Play	Power of play, games to play with infants, age-appropriate toys for infants 0-6 months. Toys and play safely for infants. Low-cost, homemade toys, quick tips for parents	Play makes children learn and explore. Engagement of the caregiver with the child during play
Maternal Postpartum Health	Postpartum maternal health. Postpartum blues, mental health checklist for new moms. Impact of maternal mental health on growing children and asking for help. Postnatal exercises and strategies to support maternal and infant mental health	Mother’s mental and physical health is a priority. It’s ok to ask for help during the postpartum phase. Timely referrals
Neonatal Development	Definition of ECD and nurturing care, domains of ECD. Description of neonatal reflexes and types of neonatal reflexes. Development milestones from 0 to 8 weeks and 3 to 6 months. Strategies for effective newborn care, infant massage, immunization, tummy time, waste disposal, and sleep modulation	ECD and holistic development. Important reflexes and developmental delays. Uniqueness of the child. Routine preventive and hygiene practices
Responsive Interactions and Attachment	Definition of attachment. Introduction to parent-child interaction. Benefits of a father’s engagement. Explaining parent-child interaction with the Barnard model (teaching and feeding interactions). Family bond	Parent-child interaction significance. Teaching interactions. Feeding interactions. Fathers’ engagement

Data collection tools

Basic Demographic Information Form

The basic demographic information form is designed to gather information pertinent to delivery outcomes, caregivers' age, education, socio-economic status, household data such as water and sanitation conditions at home, electricity and technology status, etc. This form also entails caregivers' knowledge about emergency contact numbers and child rights. Additionally, the form gathers some specific information about both the newborn and the mother, such as the mother’s height and weight, and the newborn’s gender and birth weight.

Responsive Interaction Scale

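### Confounder control is planned only for categorical outcomes, so the continuous main scores are compared between quasi-experimental groups with no covariate-adjusted model

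*Protocol article*

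**What the plan says.** The Abstract defines the main outcomes as "differences in responsive interactions and parenting confidence scores between the control and intervention groups", measured at baseline and at six months. Under Data analysis the article says "Independent sample t-test, paired test, and repeated measure ANOVA will be used to compare within and between-subject effects", and then "Multilevel logistic regression will also be performed for categorical outcomes to observe the effectiveness after controlling for the confounding factors". The significance rule is "P≤0.05 will be considered significant". No other sentence mentions confounding or a multilevel structure.

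On how the groups arise, Study design says "The field sites will be conveniently divided into two groups". The Data collection plan describes one cohort before the intervention and one with it, and the Conclusions call the design quasi-experimental. The limitations section leaves a randomised trial to the future. The Abstract alone says that sites are assigned at random.

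The data needed for adjustment are in the plan. The demographic form records caregiver age and education, "socio-economic status, household data such as water and sanitation conditions at home", and also the newborn's sex and birth weight. Both cohorts have a baseline assessment; for the control cohort the text reads "Baseline data will be collected, and they will be provided with a self-study pictorial module".

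**The concern.** The section assigns its methods by type of outcome. Confounding is recognised, but its control is attached to categorical outcomes, while the comparison in Objective 1 rests on scores. Site-level clustering is treated the same way, because the multilevel model is named only for categorical outcomes.

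Imbalance between arms is to be expected. In Table 2 the Afghan intervention site is a district hospital giving primary and secondary care, with 265 deliveries a month, inside the project's area. The Afghan control site is a comprehensive health center giving primary care, with 77 deliveries a month, outside that area. Families using two such facilities may well differ in education and means. If the scores are analysed as written, differences of this kind would be read as an effect of the parenting program.

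**Working it through.** **Inputs from the protocol article.** Pakistan 200 control and 200 intervention; Afghanistan 50 and 50. Total 200 + 200 + 50 + 50 = 500, which agrees with the stated total; 250 per arm. Alpha is 0.05, assumed two-sided because sidedness is not stated. The article gives no SD, effect size or baseline-endline correlation, so everything below is illustrative.

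**Step 1: what a confounding bias does to an unadjusted comparison.** Let b be the bias left in the arm contrast, in SD units, with no true effect.

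- Standard error, ignoring clustering: sqrt(2/250) = 0.089 SD.
- False-positive rate: Φ(b/0.089 − 1.96) + Φ(−b/0.089 − 1.96).

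| Assumed b (SD) | b / SE | False-positive rate |
|---|---|---|
| 0 | 0 | 5% |
| 0.05 | 0.56 | 8.6% |
| 0.1 | 1.12 | 20% |
| 0.2 | 2.24 | 61% |
| 0.3 | 3.35 | 92% |

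**Step 2: which analyses remove the bias.** A simulation used 2,000 runs per setting, 250 per arm, no true effect and no clustering. One covariate, standing for something like socio-economic status, affects the baseline score by 0.3 and the endline score directly by 0.3. The arms differ on it by 0.3 or 0.5 SD. The coefficient of endline on baseline is 0.3, 0.5 or 0.7.

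| Analysis | Type I error across settings |
|---|---|
| t-test on endline | 26% to 81% |
| Change score (the group-by-time test of a two-time-point repeated-measures ANOVA) | 6% to 45% |
| Endline adjusted for baseline only | 16% to 70% |
| Endline adjusted for baseline and the covariate | about 5% |

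As a check, with coefficient 0.5 and imbalance 0.3 the expected bias of the endline t-test is (0.5 × 0.3 + 0.3) × 0.3 = 0.135 SD; the simulation gave 0.135. In these scenarios it is the covariate that restores the nominal level. Baseline adjustment alone does not.

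**Step 3: baseline adjustment versus change score.** Assume a 0.3 SD gap at baseline and a within-arm slope of 0.5.

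- If the gap is stable over six months, the change score has bias 0.3 − 0.3 = 0, and the baseline-adjusted contrast has bias 0.3 − 0.5 × 0.3 = 0.15 SD.
- If the gap shrinks to 0.5 × 0.3 = 0.15 SD, the baseline-adjusted contrast has bias 0, and the change score has bias 0.15 − 0.3 = −0.15 SD.

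The article gives no ground for choosing between these, so neither analysis can be ranked first on bias alone.

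**Step 4: what can be adjusted for.** In Table 1 both Chitral districts contain one intervention and one control site, so district can enter the model within Pakistan. In Table 2 the Afghan intervention site is in Baharak and the control site in Jurm. District and arm are the same variable there, and with district terms the 100 Afghan participants would contribute nothing to the arm contrast.

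**The case against.** The strongest objection is that this is a condensed article and a statistical analysis plan may exist. Which test is primary and which covariates enter are matters commonly left to such a plan, and the sentence on regression shows that the authors mean to control confounding. This stands as far as it goes: the lack of a covariate list or a named primary test is not a fault here. The point rests on what the article does state, which is confounder control tied to one type of outcome, and not the type on which Objective 1 mainly rests. The article also calls this a feasibility study, which limits how much weight the contrast should bear but does not remove the comparison.

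Four stronger readings are tempting, and the documents do not support them.

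- **That baseline is ignored.** Repeated-measures ANOVA uses it through the group-by-time term. Only a t-test on endline scores would ignore it, and the article does not say that this is the main comparison.
- **That the change-score analysis is inferior and should be demoted.** In non-equivalent groups this is contestable, as Step 3 shows.
- **That scales would be dichotomised to obtain an adjusted result.** No such split is planned. Some outcomes may be categorical by nature: the responsive interaction scale is described as classifying behaviors, and the PHQ-9 grades depression severity.
- **That the study is non-randomised beyond dispute.** The Abstract says otherwise, and the sections must be reconciled. Even random assignment of six facilities could not be relied on to balance confounders.

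**Conclusion.** The concern holds in a limited form. As written, the plan controls for confounding and uses a multilevel structure only for categorical outcomes. The continuous main scores have no covariate-adjusted model, although the groups are described mainly as convenience-based and quasi-experimental and the covariates are collected.

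The size cannot be computed from the article. If residual confounding of 0.1 to 0.2 SD is assumed, a nominal 5% test with 250 per arm has a false-positive rate of about 20% to 61%. These figures assume two-sided testing, no clustering and full follow-up. The return to about 5% in the simulation depends on the single confounder being known and measured. In practice adjustment would reduce bias from measured differences and leave the rest.

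**What to change.** Extend the stated confounder control to the continuous scores:

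- For each score, fit a linear (mixed) model of the endline value on arm, baseline value of the same score, country, district within Pakistan only, and a short prespecified list from the demographic form (maternal age, education, socio-economic status, birth weight).
- Account for facility as far as six sites allow, and say that three facilities per arm (two in Pakistan, one in Afghanistan) limit any such adjustment.
- Report the covariate-adjusted change-score (group-by-time) result beside it, and discuss any disagreement.
- State that adjustment cannot remove unmeasured facility-level or calendar-time differences.
- Reconcile the Abstract's random assignment of sites with the convenience division and before-and-after cohorts described elsewhere.

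The cost is a few sentences in the plan and slightly more analysis work. No new data or participants are needed.
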